# Safety assessment and reporting

Safety of our intervention is paramount. Although all drugs to be used have good safety records, adverse events will be diligently sought. Before each dose is administered, participants will be asked for new symptoms or signs, with specific questions regarding skin rash, or easy bruising or bleeding.

Although remote, there is a small, finite risk of infection associated with finger prick and venous blood draws; we do not anticipate that there will be any study-related AEs. Sterile procedures will be used during blood draws and all sharps and contaminated wipes or other objects will be disposed of properly as described in the Field and Laboratory Procedures Manual.

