**Objectives**:

The **primary** **objective** of this project is to:

1. Determine whether IPT with SP + AZ is safe and whether it decreases the incidence of low birth weight (LBW; <2500 g) compared to standard treatment (i.e. a single treatment course of SP and chloroquine at booking, in conjunction with ITN use).

**Secondary objectives** of the study include:

1. To compare mean birth weight of babies born to women on SP+AZ and controls.
2. To examine the effect of SP + AZ on prevalence of *P falciparum* at delivery in peripheral, placental and cord blood films and on placental histology, and at second visit by PCR only in peripheral blood films.
3. To compare maternal haemoglobin concentrations and anaemia prevalence and severity between groups
4. To investigate the prevalence and consequences (maternal haemoglobin, birth weight and placental pathology) of *P. vivax* infection in pregnancy
5. To study immune responses to *P. vivax* in pregnant women and non-pregnant women, with and without current *P. vivax* infection
6. To determine the incidence of symptomatic malaria by passive case detection in each group.
7. To compare the proportion of women carrying azithromycin-sensitive sexually transmitted infections at second treatment visit between groups.
8. To document the incidence and severity of Adverse Events possibly or probably associated with study medications
9. To examine the prevalence of drug resistance markers in parasites infecting women in late pregnancy
10. To measure the prevalence and antibiotic sensitivity patterns of *S. pneumoniae* in nasopharyngeal swabs collected at delivery
11. To measure the impact of IPTp on development of immunity to malaria in pregnancy
12. To document maternal, perinatal and infant mortality rates in each group.

**Schematic of Study Design**: See Appendix I

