## Potential Risks and Benefits

### Potential Risks

This study is a randomised controlled trial that will compare treatment with a full course of sulfadoxine-pyrimethamine and azithromycin (SP/AZ) at enrolment between 14-26 weeks and at two further visits at least 4 weeks apart, to a single treatment course of SP and chloroquine at first antenatal visit, and SP and AZ placebo at two subsequent visits. All women will be provided with long-lasting insecticide treated nets (ITNs). AZ has not been used extensively in PNG, but has been widely used elsewhere in developed and developing countries for treatment of STIs without evidence of adverse effects. There is a long history of use of both SP and chloroquine in pregnancy, without documented toxicity.

All drug used are usually well tolerated, however mild side effects such as nausea, diarrhoea, abdominal pain, dizziness, itching or mild rashes may occur with any of the drugs used.

Participants and their fetuses and newborn children will be monitored for the occurrence of severe adverse events, including events possibly or probably due to the study medications, by the study physicians. Details of the adverse event protocols are found in Section 9.2

In order to evaluate the effect of the drug intervention on malaria infection, haemoglobin concentrations and pregnancy outcome, blood samples will be taken at enrolment (10 ml) and at subsequent treatment visits (finger prick- 250 ml) and at delivery (10 ml). For a subset of women, an additional 5 ml venous sample (instead of a finger prick) will be taken at 28-34 weeks, for studies of immune responses to *P. vivax* in pregnancy as part of the PregVax Consortium. For a subset of 200 participating women (and 50 non-pregnant community controls), we will collect a further blood sample (10 ml) at 3 months post partum, for studies of P Vivax immunology. At delivery heel prick blood sample will also be collected from each baby. Although remote, there is a small, finite risk of infection associated with finger prick and venous blood draws. However, the PNGIMR has conducted many studies involving routine finger prick and venous blood sampling from the study populations and based on our experience from these studies, very few if any study-related adverse events, as defined below, have occurred or been reported to us.

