## Objectives

The **primary** **objective** of this proposal is to determine whether the administration of IPTp with SP plus AZ results in a significant decrease in the proportion of infants born with LBW. Key secondary objectives will include increases in mean birth weight and reduction in the incidence of malaria parasitemia, anaemia and sexually transmitted infections in participating women. Together, these will determine whether SP/AZ causes significant improvements in maternal and child health. This will be the first evaluation of IPTp with SP AZ outside Africa and in a setting in which *P. vivax* infection is highly endemic.

In addition, the study will investigate if the intervention may lead to an increase in levels of drug resistance; and evaluate the effect of IPTp on the development of immunity to malaria.

**Secondary objectives** of the study include:

1. To compare mean birth weight of babies born to women on SP+AZ and controls.
2. To examine the effect of SP + AZ on prevalence of *P falciparum* at delivery in peripheral, placental and cord blood films and on placental histology, and at second visit by PCR only in peripheral blood films.
3. To compare maternal haemoglobin concentrations and anaemia prevalence and severity between groups
4. To investigate the prevalence and consequences (maternal haemoglobin, birth weight and placental pathology) of *P. vivax* infection in pregnancy
5. To compare the immune response to *P. vivax*  in pregnant and non-pregnant hosts
6. To determine the incidence of symptomatic malaria by passive case detection in each group.
7. To compare the proportion of women carrying azithromycin-sensitive sexually transmitted infections at second treatment visit between groups.
8. To document the incidence and severity of Adverse Events possibly or probably associated with study medications
9. To examine the prevalence of drug resistance markers in parasites infecting women in late pregnancy
10. To measure the prevalence and antibiotic sensitivity patterns of *S. pneumoniae* in nasopharyngeal swabs collected at delivery
11. To measure the impact of IPTp on development of immunity to malaria in pregnancy
12. To document maternal, perinatal and infant mortality rates in each group.
13. To collect maternal and child DNA to study the genetics of reproductive success, as part of a planned multinational consortium.

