# Study Design

**The study design of this research project is a randomised placebo controlled single blinded trial in pregnant women enrolled between 14 and 26 weeks’ gestation.** All women participating in this study will be followed until 6 weeks post partum. Infant survival to 1 year of age will be documented.

The intervention consists of three treatment courses of SP (3 tablets: 1500/75 mg) + AZ (2 g/day for 2 days) administered at ANC booking (provided this is between 14 and 26 weeks’ gestation) and at 2 further antenatal visits at least 4 weeks apart. Recipients in the control arm will receive a treatment course of Sp and chloroquine at enrolment, followed by AZ and SP placebos at further treatment time points. All women will be provided with a long lasting insecticide treated bed net. A block randomisation procedure will be used to allocate women to respective control and intervention groups. Among study staff, only those dispensing drug will be aware of subjects’ treatment allocation. At enrolment and at delivery a 10 ml venous blood sample will be collected to determine prevalence of malarial infections and to measure haemoglobin levels, as well as to contribute plasma, serum and peripheral blood mononuclear cells (PBMCs) for immunological analyses. At each subsequent treatment visit a 250µl finger prick blood sample will be collected for retrospective identification of malaria infection status.

At enrolment all women will have blood taken to test for syphilis by RPR and TPHA test, and women with positive tests indicating active or latent syphilis will be treated with benzathine penicillin according to standard treatment guidelines. Women will be asked to self-collect a high vaginal swab, for molecular diagnosis of STIs. Consenting women will also undergo testing for HIV (provided routinely by Modilon Hospital), and infected women will be referred to a local treatment centre providing highly active antiretroviral therapy, for prevention of mother to child transmission, and to maintain health of infected women.

From blood samples collected the prevalence and density of infections will be determined by light microscopy and PCR.

A subset of women who can attend ultrasound clinics at Modilon Hospital will have up to 3 ultrasound scans, to establish gestational age, monitor fetal growth, and measure placental blood flow.

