### Delivery and Assessment of IPTp intervention

The primary assessment of the IPTp intervention will take place at delivery.

The specific tasks to be completed by the field study team at the delivery visit are as follows:

Baby:

- Record pregnancy outcome (i.e. live birth, stillbirth, abortion)
- Record birth weight
- Collect a heel prick blood sample (200 µl)
  - Prepare thin and thick blood smears
  - Archive a portion of the blood sample for laboratory analyses
  - Measure Hb using Hemacue
- Collect a cord blood sample (approximately 10 ml)
  - Cord haemoglobin concentration
  - Archive a portion of the blood sample for laboratory analyses

Mother

- Interview and record
  - history of bednet use since previous visit
  - history of malaria treatment since previous visit
- Collect maternal peripheral blood (10 ml)
  - Prepare thin and thick blood smears
  - Measure Hb using Hemacue
  - Archive a portion of the blood sample for laboratory analyses
- Collect placental blood films and placental biopsies
- Collect a per-nasal swab

Check the health records booklet for recent health centre visits and record applicable information.

Mothers that deliver at home will be asked to visit Modilon Hospital or a participating health center within no more than a week. In these cases the following tasks will be performed:

Baby:

- Record day of birth
- Record pregnancy outcome (i.e. live birth, stillbirth, abortion)
- Record weight
- Collect a heel prick blood sample (200 µl)
  - Prepare thin and thick blood smears
  - Archive a portion of the blood sample for laboratory analyses
  - Measure Hb using Hemacue

Mother

- Interview and record
  - history of bednet use since previous visit
  - history of malaria treatment since previous visit
- Collect maternal peripheral blood (10 ml)
  - Prepare thin and thick blood smears
  - Measure Hb using Hemacue
  - Archive a portion of the blood sample for laboratory analyses

Check the health records booklet for recent health centre visits and record applicable information.

Before discharge, the field study team will schedule a 6 week post partum visit with the woman and her baby.

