## Randomisation and Blinding

### Randomisation procedures

Women will be randomized to receive SP/AZ or SP/CQ using concealed allocation. Each treatment will be randomly assigned to 4 different treatment codes, resulting in a total of 8 treatment codes (i.e. A, B, C, D, E, F, G, H). A block randomization procedure will be used, with blocks of 32, each containing 4 women assigned to each treatment code. This will help maintain concealment of allocation from study staff to the greatest extent possible.

In order to facilitate field operations independent randomization lists will be produced for each health centre / hospital. The resulting list will contain 1500 women for Modilon Hospital, 500 for each of the peripheral clinics in Madang Town, 500 each for the two field teams operating in the Madang North Coast (Mugil & Alexishafen HC) and 500 for Yagaum Health Centre. .

The lists will be generated by an independent statistician, and the code will be held by the DSMB.

Administration of second and third treatment doses will be placebo controlled.

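### Adverse events are solicited only before a dose, so course 3, one of the two SP/AZ-versus-placebo courses, has no scheduled adverse-event question after it

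*Combined protocol and SAP*

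**What the plan says.** The synopsis puts safety into the primary objective: "Determine whether IPT with SP + AZ is safe and whether it decreases the incidence of low birth weight". The Objectives section restates the primary objective as low birth weight alone and lists, among the secondary objectives, "To document the incidence and severity of Adverse Events possibly or probably associated with study medications". Adverse-event incidence is then a secondary outcome, and Section 11.1.3 analyses the side effects that are reported after any treatment.

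Section 9 promises an active search for adverse events and schedules it in one sentence: "Before each dose is administered, participants will be asked for new symptoms or signs, with specific questions regarding skin rash, or easy bruising" or bleeding. Potential Risks states what the protocol expects to see: "mild side effects such as nausea, diarrhoea, abdominal pain, dizziness, itching or mild rashes may occur with any of the drugs used".

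On exposure, the Study Design section says "The intervention consists of three treatment courses of SP" plus azithromycin, at least 4 weeks apart. The control arm receives SP and chloroquine at course 1. After that, "Administration of second and third treatment doses will be placebo controlled" (Section 6.3.1).

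The maternal interview at delivery (Section 6.1.5, facility and home) has two items, bed net use and "history of malaria treatment since previous visit". The 6-week list (Section 6.1.6) has the same two subjects. Both also have the health booklet checked.

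**The concern.** A question asked before a dose looks back at the previous course. It cannot look back at the last one. When the course without a question is an active-versus-placebo course, any drug-related events it causes fall in the SP/AZ arm only. If mild events are lost there, the SP/AZ arm loses more of them than the control arm, and the difference between arms in the adverse-event outcome shrinks.

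The analysis counts what is reported, so the way events are asked for shapes the result. Grade 1 events last under 48 hours by the plan's own definition (Section 9.1), and the remaining doses after the first of each course are taken at home. Such events are unlikely to bring a woman to a clinic unprompted.

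**Working it through.** The documents give no adverse-event rate, power or precision, so there is no stated figure to reproduce. The sample size rests on low birth weight.

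**Step 1. What each scheduled contact covers**

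| Contact | Adverse-event question in the text | Period covered |
|---|---|---|
| Before course 1 | Yes (Section 9) | Baseline, before any study drug |
| Before course 2 | Yes (Section 9) | Course 1: SP/AZ v SP/CQ |
| Before course 3 | Yes (Section 9) | Course 2: SP/AZ v placebo |
| Facility or home delivery | None listed (Section 6.1.5) | Would cover course 3: SP/AZ v placebo |
| 6 weeks post partum | None listed (Section 6.1.6) | Would cover course 3 |

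**Step 2. Share of courses followed by a solicited question**

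For any woman, the last course she receives has no question after it. The share covered is (courses − 1) / courses.

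- Full attendance: (3 − 1) / 3 = 66.7%. With 1396 women per arm, 2 × 1396 = 2792 of 3 × 1396 = 4188 courses per arm.
- Taking 90% attendance at each later treatment visit (Section 11.3 expects more than 90%): courses per woman = 1 + 2 × 0.9 = 2.8, and (2.8 − 1) / 2.8 = 64%.
- Placebo-controlled courses, full attendance: 1 of 2.

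**Step 3. What remains open after course 3**

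- Women are told at enrolment to seek care if ill (Section 6.1.4).
- Health-centre surveillance and booklet review continue (Section 6.1.7). Surveillance is centred on malaria and anaemia, and other diagnoses go to health-centre staff.
- Symptomatic women at non-treatment antenatal visits are referred, and an unscheduled-visit form is completed (Section 7.2.2).
- Mother and baby are examined at delivery (Section 6.1), and Table 2 lists a health assessment at delivery and at 6 weeks.
- Serious events, Grade 4 events and deaths are reported on site awareness, whatever the visit (Section 9.3.1).

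The last route covers severe outcomes. The others depend on the woman volunteering a symptom, on care-seeking, or on a sign still being present.

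**Step 4. Upper bound on women missed in the SP/AZ arm**

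Assumptions, none from the documents: risk p per active course, independence between courses, full capture after courses 1 and 2, no capture after course 3.

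| p | All three: 1 − (1 − p)³ | First two: 1 − (1 − p)² | Share missed |
|---|---|---|---|
| 5% | 14.3% | 9.8% | 32% |
| 10% | 27.1% | 19.0% | 30% |
| 20% | 48.8% | 36.0% | 26% |

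If instead the same women react at every course, no affected woman is missed. Any spontaneous capture after course 3 also lowers these shares.

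**Step 5. Upper bound on dilution of the arm difference**

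Assume 10% per active course (SP/CQ at course 1 included) and 5% per placebo course, otherwise as in step 4.

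- True: SP/AZ 1 − 0.9³ = 27.1%; control 1 − 0.9 × 0.95² = 18.8%; difference 8.3 points.
- Course 3 uncaptured: SP/AZ 1 − 0.9² = 19.0%; control 1 − 0.9 × 0.95 = 14.5%; difference 4.5 points.

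At most (8.3 − 4.5) / 8.3 = 46% of the difference is lost under these rates. With full spontaneous capture nothing is lost.

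**The case against.** A reader might infer that nothing at all is asked or seen after course 3. The documents do not support that: step 3 lists an interview, booklet checks, an examination and health assessments. What is missing is an adverse-event question among them.

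The task lists may also be incomplete. Those for visits 2 and 3 omit the adverse-event question too, although Section 9 requires it there, so silence in the delivery list is not proof. The case report forms and operating procedures are not in the documents and could hold such an item. This limits confidence. But at visits 2 and 3 the general rule in Section 9 fills the silence; at delivery and 6 weeks no rule does.

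A reader might also infer that the prompts miss the expected symptoms altogether. They do not. The question is open before it is specific, so it can elicit nausea or dizziness. Rash is on both lists, and rash and bruising or bleeding resemble the severe skin and petechial events named in Section 9.1. What stands is narrower: nausea, diarrhoea, abdominal pain, dizziness and itching have no specific prompt, and recall runs to at least 4 weeks.

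Finally, a question at delivery involves imperfect recall and may pick up symptoms of labour. Both points are fair, but labour symptoms should occur in both arms.

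**Conclusion.** Followed as written, the plan solicits adverse events after courses 1 and 2 and not after course 3. One of 3 courses, and one of the two placebo-controlled courses, relies on passive capture and general assessment for its non-serious events. This can undercount mild drug-related events and dilute the arm difference in that outcome.

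The size of the undercount cannot be derived from the documents. It is tempting to read the 26% to 32% in step 4 as an estimate of women missed. It is a ceiling, resting on assumed rates, independence, complete capture after two courses and none after the third.

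It is also tempting to conclude that the trial's safety finding as a whole leans toward safe. That goes too far: serious events, Grade 4 events and deaths do not depend on the pre-dose question, course 2 keeps a solicited comparison with placebo, and the primary outcome, allocation and sample size are untouched. This is a cheap improvement to a secondary outcome and not a fault that the trial cannot proceed with.

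**What to change.** 1. Add a structured adverse-event question to the existing facility-delivery and home-delivery forms, asking about the time since the last study treatment. Use the 6-week visit as fallback when delivery is missed. This wording also covers women whose last course was the first or second.
2. At every adverse-event inquiry, keep the open question and the prompts on rash, bruising and bleeding, and add the other effects named in Potential Risks: nausea, diarrhoea, abdominal pain, dizziness and itching.
3. Report solicited and spontaneous events separately and by course. Show courses 2 and 3 (SP/AZ v placebo) apart from course 1 (SP/AZ v SP/CQ).
4. If the case report forms already carry such an item, state it in Section 9 and in the visit task lists.

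The cost is one block on existing forms at existing visits, with no new visit or sample and no change in sample size. The drawbacks are recall from course 3 to delivery that may run to several weeks, and some overlap with labour symptoms. Recording the onset date of each symptom would help to separate the two.

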## Definition of Adverse Event (AE)

Possible adverse events will be assessed by the study clinician and graded in severity according to tables modified from those of the NIH Division of Microbiology and Infectious Diseases. Briefly, events will be graded in severity as:

Grade 1 (mild, self limited (<48 hours), no intervention required).

Grade 2 (moderate: some limitation in activity, some assistance possibly required; no or minimal medical intervention required).

Grade 3 (severe: marked limitation in activity; some assistance usually required; medical intervention required; hospitalization possible).

Grade 4 (life-threatening: extreme limitation in activity; significant assistance required, significant medical intervention required; hospitalization probable).

Grade 5 adverse event results in death

Any clinical event determined by the clinician to be serious or life threatening will be classed as grade 4. Such events include (but are not restricted to): seizures, coma, disseminated intravascular coagulation, desquamating skin rash suggestive of Stevens-Johnson syndrome, diffuse petechiae, paralysis, and altered behaviour suggestive of neurological disturbance.

## Definition of Serious Adverse Event (SAE)

Any untoward medical occurrence that:

- Results in death.
- Is life-threatening.
- Requires in-patient hospitalization or prolongation of existing hospitalization.
- Results in persistent or significant disability or incapacity or required intervention to prevent permanent impairment or damage.
- Is a congenital anomaly or birth defect
- Medical judgement is required in certain other circumstances such as cases requiring intensive outpatient management, blood dyscrasias or convulsions that do not require hospitalisation, and similar events.

Is to be considered a serious adverse event (SAE) and will be assessed following the PNGIMR SOPs for SAEs.

